## Abstract

**Background:**

Return of gastrointestinal (GI) function is fundamental to patient recovery after colorectal surgery and is required before patients can be discharged from hospital safely. Up to 40% of patients suffer delayed return of GI function after colorectal surgery, causing nausea, vomiting and abdominal discomfort, resulting in longer hospital stay. Small, randomised studies have suggested perioperative intravenous (IV) lidocaine, which has analgesic and anti-inflammatory effects, may accelerate return of GI function after colorectal surgery. The ALLEGRO trial is a pragmatic effectiveness study to assess the benefit of perioperative IV lidocaine in improving return of GI function after elective minimally invasive (laparoscopic or robotic) colorectal surgery.

**Methods:**

United Kingdom (UK) multi-centre double blind placebo-controlled randomised controlled trial in 562 patients undergoing elective minimally invasive colorectal resection. IV lidocaine or placebo will be infused for 6–12 h commencing at the start of surgery as an adjunct to usual analgesic/anaesthetic technique. The primary outcome will be return of GI function.

**Discussion:**

A 6–12-h perioperative intravenous infusion of 2% lidocaine is a cheap addition to usual anaesthetic/analgesic practice in elective colorectal surgery with a low incidence of adverse side-effects. If successful in achieving quicker return of gut function for more patients, it would reduce the rate of postoperative ileus and reduce the duration of inpatient recovery, resulting in reduced pain and discomfort with faster recovery and discharge from hospital. Since colorectal surgery is a common procedure undertaken in every acute hospital in the UK, a reduced length of stay and reduced rate of postoperative ileus would accrue significant cost savings for the National Health Service (NHS).

**Trial registration:**

EudraCT Number 2017-003835-12; REC Number 17/WS/0210 the trial was prospectively registered (ISRCTN Number: ISRCTN52352431); date of registration 13 June 2018; date of enrolment of first participant 14 August 2018.

## Administrative information

Note: the numbers in curly brackets in this protocol refer to SPIRIT checklist item numbers. The order of the items has been modified to group similar items (see http://www.equator-network.org/reporting-guidelines/spirit-2013-statement-defining-standard-protocol-items-for-clinical-trials/).

## Introduction

### Background and rationale {6a}

Approximately 30,000 patients per year undergo colonic surgery in the UK. Discharge from hospital after colectomy is inextricably linked to recovery of gastrointestinal (GI) function. Surgery to remove part of the colon and/or rectum causes unavoidable interruption of normal gut propulsive contraction, and almost no patients are discharged from hospital before GI function recovers. With modern care, most patients undergoing laparoscopic colectomy are independently mobile, requiring no or minimal analgesia, and free from intravenous fluids and invasive monitoring (e.g. urinary catheters) within 48–72 h. However, less than half will have regained GI function by this time point, and 10–20% will go on to suffer substantial delay to return of GI function (aka postoperative ileus) characterised by nausea, vomiting, complete constipation and abdominal distension. This pathophysiology is complex and involves interaction of endogenous factors (including pain pathways, host endocrine- and inflammation-mediated stress responses, exaggerated sympathetic autonomic activity and endogenous opioids) and exogenous factors (bowel handling during surgery, opioid analgesics, anaesthetic agents, immobility). Usually self-limiting, it prolongs hospital stay by a few days in most cases but can last up to 10 days if severe [1]. Affected patients cannot tolerate oral intake due to nausea and vomiting and require inpatient support with intravenous fluids and ongoing opioid analgesia. Although GI transit is absent, digestive fluid continues to be secreted but not absorbed (bile, gastric acid, pancreatic enzymes) causing vomiting, dehydration and progressive abdominal distension. Many patients require decompression of the fluid-distended gut by insertion of a nasogastric tube, a very uncomfortable experience that some patients rate the worst part of their postoperative recovery. Furthermore, in an increasingly elderly and frail population, postoperative ileus can contribute to development of other major complications including pulmonary aspiration, pneumonia and acute kidney impairment [2–4]. In the previous era of open colorectal surgery, many surgeons regarded delayed return of gut function as a “normal” part of a prolonged post-operative recovery. Accordingly, the true prevalence was seldom recorded; best estimates suggest it affected up to 40% of cases. However, in the last decade, minimally invasive surgical techniques (laparoscopic and robotic “key-hole” surgery) and evidence-based “Enhanced Recovery” perioperative management care pathways have reduced average length of hospital stay from 9 days to 4–6 days and have of themselves reduced the prevalence of delayed return of gut function. The success of these techniques in accelerating recovery has highlighted that delayed return of GI function has become the main barrier to discharge for a significant proportion of minimally invasive colectomy patients.

There is no specific therapy for postoperative ileus; treatment is supportive until GI function returns spontaneously. Alvimopan (Entereg®) is a selective μ-opioid receptor antagonist evaluated in a number of North American randomised controlled trials (RCTs) where it has been shown to be of benefit in reducing incidence of postoperative ileus [5]. However, it has not gained widespread use due to cost and concerns regarding its cardiac side-effect profile and is not licensed for use in the UK.

Lidocaine, familiar as a local anaesthetic, has analgesic and anti-inflammatory effects when administered systemically by intravenous (IV) infusion and hence has been repurposed as an anaesthetic adjunct in abdominal surgery. Studies in various surgical procedures have shown reduced early postoperative pain scores and reduced opioid analgesia requirements. There also seems to be a consistent benefit on measures of GI function recovery, including time to first flatus, time to first bowel movement, postoperative nausea and risk of postoperative ileus. However, the limitation of meta-analysis in this area is the considerable heterogeneity of studies included: a variety of surgical procedures, a mix of open and laparoscopic techniques, inconsistent lidocaine dose/treatment duration, inconsistent perioperative management protocols and study endpoints [6–8]. There are only three published RCTs of intravenous lidocaine in laparoscopic colectomy, comprising a total of 181 patients. Two were conducted in Europe and reported length of stay consistent with modern NHS practice (3 to 5 days) [9, 10]. Both studies reported reduced analgesic requirements, faster return of gut function and a 1-day reduction in median length of stay. The third study was conducted in South Korea and found a trend towards faster GI recovery but no statistically significant benefit. However, perioperative management practices were not consistent with NHS norms and the excessive median length of stay of 9 days makes this study difficult to interpret [11].

There is some controversy in the use of perioperative IV lidocaine. Although it has many advocates in the anaesthetic community, there is a risk of fatal toxicity in overdose. The dose and duration of IV lidocaine used in ALLEGRO is at the lower threshold of the known therapeutic range; the greatest risk of toxicity is from human error in drug administration. Although guidelines for use of IV lidocaine were published recently (subsequent to the start of the ALLEGRO study), an accompanying editorial was not supportive [12, 13]. As emphasised in the ensuing journal correspondence, there is scant randomised evidence from large trials, and ALLEGRO is the only adequately powered trial of IV lidocaine currently recruiting [14].

Intravenous lidocaine is cheap, familiar and easy to administer within existing NHS perioperative practice. If effective in improving return of GI function postoperatively it would achieve faster recovery and shorter hospital stay for patients undergoing colorectal surgery, resulting in a major cost saving for the NHS from a common (and resource-intensive) surgical intervention.

### Objectives {7}

#### Primary objective

The aim of the study is to measure whether perioperative intravenous lidocaine achieves faster return of GI function for more patients after laparoscopic colectomy. The primary objective is to compare the proportion of participants randomised to IV lidocaine or placebo that have achieved return of gut function at 72 h post-operatively (GI-3 recovery endpoint).

#### Secondary objectives

The secondary objectives are to compare the proportion of participants randomised to IV lidocaine or placebo in respect of:
GI-2 recovery endpointThe rate of prolonged postoperative ileusPostoperative nausea and vomitingAnalgesia requirementsQuality of postoperative recovery using multi-dimensional patient-reported outcome tools and quality of life tools.

Additional secondary objectives include assessing whether perioperative intravenous lidocaine during colorectal surgery is cost-effective relative to current standard of care (colorectal surgery without intravenous lidocaine) and measuring the impact of variation in peri-operative care from Enhanced Recovery After Surgery guidelines.

The tertiary objectives are to compare the proportion of participants randomised to IV lidocaine or placebo in respect of:
Total length of stay30- and 90-day mortalityUnplanned re-admissions within 30 days of hospital dischargeReoperation/major complications (Clavien-Dindo classification grade 3 and above) [15]Qualitative analysis of recovery beyond hospital (General Practitioner (GP) visits, district nurse visits).

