### Data collection and management

#### Plans for assessment and collection of outcomes {18a}

Data are collected at baseline and at 1, 2, 3, 4, 5, 6 and 7 days after surgery, at discharge from hospital and at 30 and 90 days after surgery. The schedule for data collection is summarised in Table 1.

**Table 1 Tab1:** Schedule for data collection

Assessment	Recruitment/baseline	POD 1	POD 2	POD 3	Daily from POD 4 until discharge	POD 7	Discharge	30 days	90 days
Assessment of eligibility criteria	✓								
Written informed consent	✓								
Pregnancy test (where applicable)									
Demographic data, contact details	✓								
Clinical history/past medical history	✓								
Drug history esp. laxatives	✓								
Height	✓								
Weight	✓	✓							
p-POSSUM	✓	✓ (part)						✓ (part)	
Operation type		✓							
Duration of operation		✓							
Blood loss (ml)^a^		✓							
OBAS score	✓	✓	✓	✓	✓	✓			
QoR score	✓	✓	✓	✓	✓	✓		✓	
PONV score		✓	✓	✓	✓				
EQ-5D-5L	✓	✓	✓	✓	✓	✓		✓	✓
CRP^b^	✓		✓	✓					
Time to first flatus			✓	✓	✓				
Time to first bowel movement			✓	✓	✓				
Time to tolerating solid food			✓	✓	✓				
antiemetic dose total up to 72 h							✓		
Total number of episodes vomiting		✓	✓	✓					
Total opioid consumption in-hospital up to 72 h							✓		
ERAS protocol compliance		✓	✓	✓					
Achievement of medical criteria for discharge Y/N				✓	✓				
Patient-reported readiness for discharge				✓	✓				
Length of stay (days)							✓		
Complications							✓	✓	
Unplanned readmissions								✓	
Mortality							✓	✓	✓
Adverse events		✓	✓	✓	✓	✓		✓	
Concomitant medications	✓	✓	✓	✓	✓	✓		✓	

^a^Millilitres

^b^C-reactive protein

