#### Plans to promote participant retention and complete follow-up {18b}

Data are collected at routine clinic/hospital appointments and in hospital during postoperative recovery. It is highly unlikely that any patient will be discharged from hospital prior to achieving the primary endpoint; in such cases, this will be collected by phone at 7 days. For the participant reported outcomes collected (by telephone) at 7, 30 and 90 days after surgery, there is an acceptable visit window within which this data can be collected. We will aim to collect outcome data on all participants randomised, regardless of whether or not they received the intravenous lidocaine/placebo. There are no additional plans to enhance retention in ALLEGRO.

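### Unplanned readmission is defined over 30 days from discharge but scheduled for collection once, 30 days after surgery, so the defined rate is under-counted, most in long stays (minor point)

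*Protocol article*

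**What the plan says.** The tertiary objectives, listed under Secondary objectives, compare the arms on unplanned "re-admissions within 30 days of hospital" discharge. The clock for this outcome starts at discharge.

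Section {18a} sets the later assessments "at discharge from hospital and at 30 and 90 days after surgery". The clock for those contacts starts at surgery. In Table 1 the row "Unplanned readmissions" has one tick, in the 30-day column. The discharge and 90-day cells are blank. The only rows ticked at 90 days are EQ-5D-5L and mortality.

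Four other places bear on the point:
- Section {18b} says of the telephone-collected participant-reported outcomes that "there is an acceptable visit window within which this data can be collected". It gives no width.
- The outcome list in {12} has no separate readmission outcome. It includes readmission days in total length of stay and plans a cost analysis to 90 days from hospital records, GP visits and participant report.
- Section {20a} refers to Table 1 for the hospital-record resource data.
- Section {22} ends adverse event recording at postoperative day 30, so that route does not extend past the 30-day contact.

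**The concern.** The definition and the collection schedule start from different dates, and both are printed. An analysis plan cannot repair this by itself, because it cannot count events that nobody recorded.

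Two consequences follow if the printed schedule is all there is. First, the reported figure would carry the label of 30 days from discharge without being that figure, and it would be too low in both arms. Second, the unobserved part of the window grows by one day for each extra day of stay, and length of stay is something lidocaine is expected to change. The Background cites two European trials that found "a 1-day reduction in median length of stay". An arm with shorter stays is watched for longer after discharge, so it would show slightly more counted readmissions at equal true rates. Readmission is also the natural check on whether earlier discharge was premature, so the direction of any artefact is worth knowing.

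**Working it through.** The protocol gives no readmission rate and no calculation for this outcome, so there is no figure of its own to reproduce. The sample size enters only through 562/2 = 281 per arm.

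**Inputs from the protocol**
- Defined window: 30 days from discharge (tertiary objectives).
- Scheduled collection: day 30 after surgery ({18a} and Table 1).
- Typical stay: modern care has "reduced average length of hospital stay from 9 days to 4–6 days" (Background). I treat this as days from surgery to discharge, L.
- Long stay: L = 10 is illustrative. The Background says severe ileus "can last up to 10 days if severe", which describes the ileus and not the whole stay.
- Prolonged ileus: 20% v 10%, the power scenario in {14}.

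**Step 1: time observed.** Observed days after discharge = 30 − L. The defined window closes on postoperative day 30 + L.

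| L (days) | Observed days | Share of window | Window closes, postoperative day |
|---|---|---|---|
| 3 | 27 | 90% | 33 |
| 4 | 26 | 87% | 34 |
| 5 | 25 | 83% | 35 |
| 6 | 24 | 80% | 36 |
| 10 | 20 | 67% | 40 |
| 20 | 10 | 33% | 50 |

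**Step 2: share of events missed.** This depends on when readmissions occur, which the protocol does not say. Two assumed patterns, where F(t) is the share of 30-day readmissions occurring by day t after discharge:
- Even: F(t) = t/30. Missed at L = 4 to 6: 13% to 20%. Missed at L = 10: 33%.
- Front-loaded (exponential, mean 10 days): F(t) = (1 − exp(−t/10)) / (1 − exp(−3)). Missed at L = 4 to 6: 3% to 4%. Missed at L = 10: 9%.

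**Step 3: difference between arms at equal true rates.** Further assumptions: a true rate of 10% in both arms, a 12-day stay for patients with prolonged ileus (F(18)), and for all others 5 days on placebo (F(25)) and 4 days on lidocaine (F(26)).
- Even, placebo: 10% × (0.8 × 25/30 + 0.2 × 18/30) = 7.87%.
- Even, lidocaine: 10% × (0.9 × 26/30 + 0.1 × 18/30) = 8.40%. Difference 0.53 points.
- Front-loaded, placebo: 10% × (0.8 × 0.966 + 0.2 × 0.878) = 9.48%.
- Front-loaded, lidocaine: 10% × (0.9 × 0.974 + 0.1 × 0.878) = 9.65%. Difference 0.16 points.

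The difference is proportional to the true rate. Over 5% to 15% it is 0.27 to 0.80 points (even) or 0.08 to 0.24 points (front-loaded).

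**Step 4: against sampling error.** At 10% with 281 per arm, the standard error of the difference is √(2 × 0.1 × 0.9 / 281) = 0.0253, about 2.5 points. The artefact is 0.53/2.5 ≈ 0.2 of a standard error (even) or 0.16/2.5 ≈ 0.06 (front-loaded).

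**Step 5: would later collection suffice?** Collection on day 90 covers the whole window when 30 + L ≤ 90, that is for stays up to 60 days.

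**The case against.** The strongest reply is that the printed schedule may not be the whole of data collection. Section {18a} says Table 1 is a summary, and the full protocol is a supplement that is not shown here. The table is visibly incomplete: the cost analysis uses GP visits and participant-reported data to 90 days, and Table 1 has no row for either. Total length of stay includes readmission days, so some readmission information must be held. A telephone contact made 3 to 6 days late, if the visit window allows it, would cover stays of 3 to 6 days.

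This much stands: a reader might infer that the outcome cannot be completed for any patient, and the article does not support that. What remains is that none of these routes is stated to supply dated readmissions to 30 days after discharge. The visit window has no stated width and is described for participant-reported outcomes. Section {20a} points back to Table 1 for the hospital-record items, and Table 1 has no readmission item after day 30. Recovery by these routes would be incidental and possibly uneven.

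A second reply is that the between-arm effect is negligible. That also stands. A reader might infer a material bias against lidocaine on a safety check. Even the least favourable case above combines a 1-day shorter stay for everyone without prolonged ileus with a halving of prolonged ileus, and still gives well under one standard error. Readmissions caused by premature discharge would plausibly come early, which is the front-loaded case with the smaller losses.

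**Conclusion.** The mismatch is real and is in the text. Collection on the printed schedule yields a count to postoperative day 30, not the stated rate over 30 days from discharge. At stays of 4 to 6 days, 4 to 6 days of the window go unseen, and at a 10-day stay 10 days do. These day counts rest only on the contact taking place on its scheduled day. The share of events lost (3% to 20% at typical stays) and the between-arm difference (about 0.1 to 0.8 points) rest on assumed rates, timing and stays that the protocol does not give.

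The point is minor. The objective is tertiary, the distortion between arms could hardly change a conclusion, and the primary outcome and sample size are untouched. It merits correction because the label would be wrong and the undercount is greatest in patients with long stays, including those with prolonged ileus.

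It is also tempting to think that counting from surgery removes the arm difference. It does not: the same events are counted, so the model above still gives 7.87% v 8.40%. Only the label becomes accurate.

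**What to change.** **Preferred.** Keep the discharge-based definition. Record unplanned readmissions with their dates at the existing 90-day contact or from hospital records, and count those within 30 days of each patient's own discharge. This is complete for stays up to 60 days. For participants already past day 90, use hospital records, since recruitment began in August 2018 and a new item cannot reach them prospectively. Add the item to Table 1.

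**If that is not done.** Relabel the outcome as unplanned readmission within 30 days of surgery, so that it matches what is collected, and state that time at risk after discharge still depends on length of stay.

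**Cost.** The preferred change needs one more dated item, longer participant recall (which hospital records can check) and a protocol amendment with the approvals described in {25}. The fallback costs a sentence of definition and one of caveat, and gives up the discharge-based rate.

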### Trial design {eight}

The trial design is as follows: parallel group effectiveness trial of perioperative IV lidocaine infusion versus placebo (0.9% NaCl) with 1:1 allocation.

## Methods: participants, interventions and outcomes

### Study setting {9}

We are recruiting patients in 25–30 colorectal surgery units across the UK. A list of study sites can be obtained from the trial website (https://w3.abdn.ac.uk/hsru/ALLEGRO/Public/Public/index.cshtml) and will be included in the final report from the study.

### Eligibility criteria {10}

#### Inclusion criteria

Patients scheduled for elective minimally invasive (laparoscopic or robotic) colorectal resection for colorectal cancer, benign polyps, benign stricture or diverticular disease at participating UK colorectal surgical units. Right hemicolectomy, extended right hemicolectomy, left colectomy, sigmoid colectomy, subtotal colectomy with ileosigmoid or ileorectal anastomosis and high anterior resection are eligible.

#### Exclusion criteria

Planned epidural anaesthesiaPlanned regional or local continuous infusion of lidocaine at the same time as lidocaine infusionPlanned open surgeryCurrent pregnancyBreastfeedingAge < 18 yearsPatients lacking capacity to give informed consentKnown or suspected allergy to lidocaine or amide-type local anaestheticsCurrent complete heart blockCurrent severe liver dysfunction (Child’s A or greater)Current renal failure (estimated glomerular filtration rate (eGFR) < 30)Patients participating in the active intervention phase of another therapeutic clinical trial (or other interventional trial) unless a co-enrolment agreement is in placePatients having surgery for indications other than those noted aboveRectal cancer below the peritoneal reflection in which total mesorectal excision is plannedRectal cancer patients who have received any neoadjuvant radiotherapyA preoperative surgical plan to form any new stoma during the primary procedure

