#### Relevant concomitant care permitted or prohibited during the trial {11d}

Concomitant continuous infusions of local anaesthetic agents are prohibited to prevent cumulative systemic toxicity; hence, planned epidurals or continuous infusion of local anaesthetic via wound catheters are both exclusion criteria.

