### Recruitment {15}

Eligible individuals are identified by their usual clinical team from planned elective operating lists and given a patient information sheet. Eligibility is confirmed, consent received, baseline details collected, and randomisation performed pre-operatively, where possible, at routine hospital visits.

As noted above (in the “Who will take informed consent? {26a}” section) where a face-to-face visit is not possible to carry out the recruitment procedures, participants can complete the consent form at home and either post it back to the research team or bring it into hospital with them when they are admitted for surgery. In such cases, eligibility is confirmed, baseline details collected, and randomisation performed pre-operatively.

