In common with many studies, recruitment to ALLEGRO was halted by the COVID pandemic. However, the essential nature of the surgery (predominantly for cancer) meant that eligible cases restarted relatively quickly, and the original design of the study, which had aimed to integrate trial processes with existing hospital contact points in the surgical patient pathway (outpatient clinics, preassessment appointments) meant that no change of trial design was required to meet COVID restrictions. However, we did alter some processes around consent and giving patient information to allow research teams to have a consent discussion by telephone with participants subsequently returning the completed consent form by post.

The need to randomise participants before date of operation in order to have the trial drug dispensed from clinical trial pharmacies ready for the start of surgery has resulted in unanticipated issues in some cases resulting in a relatively high number of post-randomisation exclusions. The main reasons for these are change in planned type of surgery (particularly open rather than minimally invasive technique; a preoperative decision to make a new stoma) or change in anaesthetic technique (particularly decision to use an epidural) made on the morning of surgery. This is a challenging area for trial teams: it can be difficult to know which surgical/anaesthetic staff are undertaking an operating list until relatively late, there may be nuances about the planned operation known only to the operating surgeon and not always stated on the operating theatre list and there is varying integration of research nurses within the participating surgical/anaesthetic teams. At the current rate, we anticipate approximately 20–25 post randomisation exclusions; the appropriate number of cases will be added to the study to achieve the target sample size of 562 cases.

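### The exclusion list bars a concurrent continuous infusion of lidocaine only, although the concomitant-care section says wound-catheter infusion of any local anaesthetic is an exclusion criterion

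*Protocol article*

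**What the plan says.** Two sections of the protocol article deal with local anaesthetic given by continuous infusion alongside the trial drug.

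- **Eligibility criteria {10}, Exclusion criteria.** Planned epidural anaesthesia is one item. A separate item excludes a planned "regional or local continuous infusion of lidocaine at the same time as lidocaine" infusion. The route is broad (regional or local), but the only agent named is lidocaine.
- **Relevant concomitant care permitted or prohibited during the trial {11d}.** The rule here covers the drug class: "Concomitant continuous infusions of local anaesthetic agents are prohibited to prevent cumulative systemic toxicity". The section then draws the consequence for eligibility, stating that "planned epidurals or continuous infusion of local anaesthetic via wound catheters are both exclusion criteria".

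Under Recruitment {15}, eligibility is checked before allocation: "Eligibility is confirmed, consent received, baseline details collected, and randomisation performed pre-operatively", where possible at routine hospital visits.

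**The concern.** Section {11d} does more than prohibit a co-medication. It also makes a factual statement about what the exclusion list contains. The epidural half of that statement is true. The wound-catheter half is true only if the catheter is to deliver lidocaine. For any other local anaesthetic, the list has no item that excludes the patient.

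The stated reason for the rule is cumulative systemic toxicity, and {11d} gives that reason for local anaesthetic agents generally. The listed criterion is therefore narrower than the purpose the document itself assigns to it. What is at stake is consistency at screening: someone working from the list and someone working from {11d} would classify the same patient differently. The design decision, that no other local anaesthetic infusion should run alongside the trial drug, is clear and is not criticised.

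**Working it through.** No figure in the document depends on this rule, so there is nothing to compute. The check compares the two sections case by case for an infusion that is planned before randomisation and would overlap with the study infusion.

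| Planned technique | Exclusion criteria {10} | Concomitant care {11d} | Result |
|---|---|---|---|
| Epidural | Excluded (own item) | Named as an exclusion | Agree |
| Wound catheter, lidocaine | Excluded (local infusion of lidocaine) | Named as an exclusion | Agree |
| Wound catheter, another local anaesthetic | No item applies | Named as an exclusion | **Contradiction** |
| Other regional catheter, lidocaine | Excluded (regional infusion of lidocaine) | Prohibited during the study infusion; not named as an exclusion | Compatible |
| Other regional catheter, another local anaesthetic | No item applies | Prohibited during the study infusion; not named as an exclusion | Not a contradiction; the list is narrower than the prohibition |

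Three steps support the third row.

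1. *Does another listed item catch this patient?* No. The epidural item concerns a different route. The only other item that mentions local anaesthetics beyond lidocaine is the allergy criterion, which has nothing to do with concurrent infusions.
2. *Could lidocaine in the list be shorthand for the class?* That is not a safe reading. The allergy criterion in the same list names lidocaine and amide-type local anaesthetics separately, so the list uses class wording where it means a class. It does not do so in the infusion item.
3. *Is the agent really unrestricted in {11d}?* Yes. Both the prohibition and the restated exclusion refer to local anaesthetic without naming an agent.

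The table also shows that the two sections differ in route as well as agent. The list says regional or local; the exclusion restated in {11d} names epidurals and wound catheters only. The strict contradiction about eligibility is therefore confined to one row, the wound-catheter infusion of an agent other than lidocaine. The last row is a weaker mismatch, between what may be given during the trial and who may enter it.

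**The case against.** The strongest reply is that the document resolves the matter itself. Section {11d} bars the co-infusion, gives the reason, and says that wound-catheter infusion is an exclusion criterion, so the intended rule can be recovered and the list item looks like a drafting slip. This stands as a limit on the consequence. It does not remove the inconsistency, because the list is the natural text to screen from and it gives the wrong answer for this patient.

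A second reply is that the article condenses a fuller protocol, which is said to be available as a supplement. Sites may work from that document or from a screening form with better wording. This also stands: practice at sites cannot be judged from the article. But the point is not that something has been left out. The article states one rule in two places with different scope.

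Three stronger readings are tempting and should be resisted.

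- *That the protocol permits a second local anaesthetic to run with the study drug.* It does not. The prohibition in {11d} covers every agent, and the Interventions sections separately require continuous cardiac monitoring and immediate stopping if symptoms of toxicity appear.
- *That {11d} makes every non-epidural catheter infusion of another agent an exclusion criterion.* It names only epidurals and wound catheters. Other regional catheter infusions fall under its prohibition alone.
- *That this wording feeds the post-randomisation exclusions.* The Discussion says "we anticipate approximately 20–25 post randomisation exclusions", but the main reasons it gives are a changed surgical plan or a "change in anaesthetic technique (particularly decision to use an epidural) made on the morning of surgery". Those are late decisions, and catheter infusions are not mentioned. Nor does the document say that a patient with a planned catheter would be removed after randomisation; the team could comply with {11d} by not running the catheter alongside the study infusion. None of the expected exclusions can be attributed to this item.

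**Conclusion.** The inconsistency is real and minor. For a planned wound-catheter infusion of a local anaesthetic other than lidocaine, the exclusion list and {11d} give opposite answers on eligibility. For other regional catheter infusions of such an agent, the list is narrower than the trial's own prohibition without contradicting it.

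No size can be put on it: the document gives no frequency for these techniques and no dose or risk figure for the overlap. The primary outcome, sample size, alpha and analysis are untouched. The conclusion rests on reading the two sections literally, and on the catheter infusion being planned before randomisation and overlapping with the study infusion. Confidence is high that the wording conflicts. Nothing can be said about how sites have applied it, because the full protocol and screening form are not shown.

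**What to change.** Reword the infusion item under Exclusion criteria as: *Planned regional or local (including wound-catheter) continuous infusion of any local anaesthetic agent at the same time as the study infusion.* Use the same line at screening, before randomisation.

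This brings the list into line with the class-wide prohibition in {11d}. For regional catheters other than wound catheters it goes slightly beyond the exclusions that {11d} names, but not beyond what {11d} already prohibits. Referring to the study infusion instead of the lidocaine infusion is only an editorial clarification.

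The cost is one line in the list and the matching line used at screening. The small downside is that a few patients with such an infusion planned become ineligible at screening; the document gives no basis for saying how many.
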